## Outcome Measures

The participant timeline is presented in Table 1.

**Table 1 Tab1:** Schedule of enrolment, intervention, and assessment

Study period	Enrolment		Allocation	Angioplasty	Post-Procedure	Follow-up				
		Index procedure								
Timepoint	*− t*_1_***	*− t*_2_†	0	Immediately after allocation	At discharge§	1 month ± 7 days On-site	6 months ± 30 days On-site	12 months ± 45 days On-site	24 months ± 60 days On-site	36 months ± 60 days On-site
ENROLMENT										
Eligibility screen	X									
Informed consent	X									
Allocation			X							
INTERVENTION										
Intraluminal guide wire crossing^‡^		X								
Pre-dilation**		X								
Sirolimus-coated balloon angioplasty				X						
Standard balloon angioplasty				X						
ASSESSMENT										
Demographic data	X									
Physical examination^††^	X				X	X	X	X	X	X
Laboratory examination^‡‡^	X									
Medical history	X									
Concomitant medication	X				X	X	X	X	X	X
Angiography		X		X						
Duplex ultrasonography^§§^					X	X	X	X	X	X
ABI	X				X	X	X	X	X	X
TBI	X				X	X	X	X	X	X
Rutherford category	X					X	X	X	X	X
Wound evaluation	X				X	X	X	X	X	X
Walking distance (Participant self-assessment***)	X					X	X	X	X	X
VascuQuol Score	X					X	X	X	X	X
EQ-5D-3L index	X					X	X	X	X	X
AE/SAE		X		X	X	X	X	X	X	X

ABI, ankle-brachial index; AE, adverse event; EQ-5D-3L index, European quality of life 5 dimensions 3 level index; SAE, severe adverse event; TBI, toe-brachial index

^*^At baseline

^†^During index procedure

^‡^Successful intraluminal guidewire crossing of the lesion

^§^Within two working days after index procedure and before discharge

^**^Pre-dilation with residual diameter stenosis < 50% (by angiographic visual estimate) and without flow limiting dissection

^††^Including blood pressure and heart rate

^‡‡^Creatinine, platelets, white blood cell count, pregnancy test were appropriate

^§§^Duplex ultrasonography should also be performed before and after any target vessel revascularization. Adjudication by core laboratory at 6, 12, and 24 months

***Participant self-assessment of maximum walking distance should be performed before completion of the questionnaires

### Primary Outcome

Primary efficacy outcome is the composite of limb salvage and primary patency at 6 months (Kaplan–Meier estimate). Primary patency is defined as the absence of target lesion occlusion with restoration of in-line flow to the ankle [3] without repeat clinically driven target lesion revascularization (TLR). TLR is considered clinically driven in case of ≥ 70% diameter stenosis (by quantitative angiography conducted by the core laboratory) and deterioration of Rutherford category and/or deterioration or persistence of wounds according to the WIfI classification wound component score.

Primary patency as assessed with duplex ultrasonography (DUS) must be confirmed by the independent, blinded core laboratory. DUS images and medical records will be made available for review by the clinical events committee upon request.

### Secondary Outcomes

*Key secondary safety outcome* is the composite of major adverse limb events and perioperative all-cause death (MALE-POD) at 30 days (non-inferiority). MALE is defined as above the ankle amputation or major intervention (new bypass graft, interposition graft revision, or thrombectomy/thrombolysis) of the target limb that involves infra-popliteal arteries.

### Further Secondary Outcomes

Device success (deployment of the study device according to manufacturer’s instructions of use).Technical success (device success and absence of target lesion occlusion with restoration of in-line flow to the ankle).Procedural success (technical success and absence of major adverse events (MALE-POD, myocardial infarction, stroke) within 72 h of the index procedure) [21]Composite of limb salvage and primary patency at 1, 12, 24, and 36 monthsClinically driven TLR/target vessel revascularization (TVR) at 1, 6, 12, 24, and 36 monthsPrimary/secondary target lesion patency at 1, 6, 12, 24, and 36 monthsTarget lesion reocclusion at 1, 6, 12, 24, and 36 monthsAmputation-free survival at 1, 6, 12, 24, and 36 monthsAll-cause death at 1, 6, 12, 24, and 36 monthsChange in Rutherford classification at 1, 6, 12, 24, and 36 monthsChange in ankle-/toe-brachial index at 1, 6, 12, 24, and 36 monthsPrimary/secondary clinical improvement at 1, 6, 12, 24, and 36 monthsChange in EQ-5D-3L index/VascuQuol Score at 1, 6, 12, 24, and 36 monthsChange in self-reported walking distance at 1, 6, 12, 24, and 36 monthsWound healing at 1, 6, 12, 24, and 36 monthsDays of hospitalization at 1, 6, 12, 24, and 36 months

Angiographic imaging and DUS at 6, 12, and 24 months will be adjudicated by a blinded core laboratory.

### Statistics

Based on results from the Lutonix BTK trial and the ACOART-BTK study [13, 22], we assumed a 55% rate of primary patency in the control group. Given a minimally clinical important difference of 20% (benefit from the study intervention) to be detected with 80% probability at a two-sided 5% level of significance and considering 20% of drop-out, 230 participants (115 in each group) need to be recruited. As incidences of 30-day freedom from MALE-POD in the Lutonix BTK trial were about 99% in both groups, 230 participants are also sufficient to provide 90% power to prove non-inferiority of sirolimus-coated balloon angioplasty to POBA regarding the key secondary safety endpoint at a one-sided 2.5% significance level. The primary efficacy endpoint will be assessed with Kaplan–Meier analysis applying the log-rank test. The key secondary safety endpoint will be assessed with the Farrington–Manning test. The non-inferiority margin is sat at 10%. Further secondary endpoints will be compared using the two-sided t-test, the Mann–Whitney *U* test, and the log-rank test where appropriate. Subgroup analysis will be conducted to consider diabetes, lesion length, and distal run-off. Analyses will be based on data from the intention-to-treat (ITT) study population (enrolled participants, irrespective of whether or not they underwent the allocated intervention). Primary outcome and key secondary outcome will additionally be analysed based on the modified ITT study population (participants who received the assigned treatment).

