**Study design:**

The randomized controlled, single-blinded, multicentre, investigator-initiated study aims to enrol 230 participants with CLTI and infra-popliteal occlusions at up to 25 centres. Patients will be randomized in a 1:1 ratio to either sirolimus-coated balloon angioplasty or to plain old balloon angioplasty (POBA). Bailout stenting in case of flow-limiting dissection or ≥ 50% residual diameter stenosis is permitted.

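### Change in ABI/TBI, EQ-5D-3L, VascuQuol and walking distance is to be compared without baseline as a covariate: valid, but generally less precise than it need be (minor)

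*Protocol article*

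**What the plan says.** The protocol article's Statistics section gives one sentence to the whole group. It begins "Further secondary endpoints will be compared using the two-sided t-test" and goes on to name a rank test (Mann–Whitney) and a log-rank test, each for the endpoints it suits. The Further Secondary Outcomes section defines ABI and TBI, the EQ-5D-3L index and VascuQuol score, and self-reported walking distance as changes, each at 1, 6, 12, 24 and 36 months. Table 1 marks every one of these measures in the enrolment column, which its footnote identifies as baseline.

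The article names no analysis of covariance, mixed model or other baseline-adjusted method. Baseline enters these comparisons only by subtraction.

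**The concern.** A log-rank test does not suit a change score, so the named tests reduce to a t-test or a Mann–Whitney test on change. Both compare two groups without a covariate. Subtraction fixes the weight given to baseline at 1, whereas the best weight is the slope of follow-up on baseline. When that slope is below 1, the arm that starts lower by chance tends to show the larger gain, and the treatment contrast carries avoidable noise.

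The sample size was set for patency, with a check for the 30-day safety composite. No power is claimed for the functional and quality-of-life outcomes, so their precision depends on how they are analysed.

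**Working it through.** **The plan's own figure.** The plan gives no number for these outcomes. Its only related calculation is the sample size for the primary endpoint. There, "we assumed a 55% rate of primary patency in the control group" is the starting point. The other inputs are a 20-point difference, 80% power, two-sided α = 0.05 and an allowance of one fifth for drop-out. The article's result is a total of 230, or 115 per arm.
- Hazard ratio: ln(0.75)/ln(0.55) = 0.481. Freedman's formula then gives 64 events.
- Mean event proportion: (0.45 + 0.25)/2 = 0.35.
- Total: 64/0.35 = 182.9, and 182.9/0.8 = 228.6, close to the stated 230.

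The stated total is reproduced. It concerns patency and neither supports nor weakens the point here.

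**Inputs for the check.** The documents give no SD and no baseline–follow-up correlation r for any of these outcomes. I assume r = 0.3 to 0.8 and, at first, equal SDs at baseline and follow-up.

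**Formulas, in units of the common variance.**
- Change score: 2(1 − r).
- ANCOVA: 1 − r².
- Ratio of ANCOVA to change: (1 − r²)/[2(1 − r)] = (1 + r)/2.
- Shift of the change-score contrast when the arms differ at baseline by d SD: (r − 1)d.

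| r | Change | ANCOVA | Ratio | Patients needed by change-score test relative to ANCOVA | ANCOVA power where change-score t-test has 80% | Shift for d = 0.2 SD |
|---|---|---|---|---|---|---|
| 0.3 | 1.40 | 0.91 | 0.65 | 1/0.65 = 1.54 | 93.5% | −0.14 SD |
| 0.5 | 1.00 | 0.75 | 0.75 | 1/0.75 = 1.33 | 89.9% | −0.10 SD |
| 0.7 | 0.60 | 0.51 | 0.85 | 1/0.85 = 1.18 | 86.0% | −0.06 SD |
| 0.8 | 0.40 | 0.36 | 0.90 | 1/0.90 = 1.11 | 84.0% | −0.04 SD |

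At r = 0.3, subtracting baseline (1.40) is noisier than ignoring it (1.00).

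**Is d = 0.2 SD plausible?** The standard error of a chance baseline difference is √(2/115) = 0.13 SD with 115 per arm. With 92 per arm (115 × 0.8) it is √(2/92) = 0.15 SD. A difference of 0.2 SD on some of these outcomes would be unremarkable.

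**Unequal SDs.** Let the follow-up SD be k times the baseline SD. The slope of follow-up on baseline is then β = rk, and the ratio becomes k²(1 − r²)/(1 + k² − 2rk). At r = 0.5:

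| k | β | Ratio |
|---|---|---|
| 1 | 0.50 | 0.75/1.00 = 0.75 |
| 1.5 | 0.75 | 1.6875/1.75 = 0.96 |
| 2 | 1.00 | 3/3 = 1.00 |

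In general, the change score's excess variance is (1 − β)² times the baseline variance. This is never negative, so in large samples ANCOVA is never less precise. The excess vanishes at β = 1.

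**The case against.** The strongest reply is that nothing here is an error. A two-sample test on change is valid under randomisation: it is unbiased over repeated randomisation and keeps its type I error. That stands. What is lost is precision, along with accuracy conditional on the baseline difference that happens to occur.

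A second reply is that one condensed sentence covers a long list of outcomes and assigns no test to any of them, so endpoint-level models may sit in the unseen SAP. In part this stands: testing change separately at each visit is an inference, though a natural one from two-sample tests and five listed time points. But the article does name the tests, and none of them adjusts for baseline. It is a stated choice rather than a gap.

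A third reply is that the size is unknown. That stands too. Entry at Rutherford category 4 to 6 could compress baseline walking distance and revascularisation could widen it, which pushes k up and can remove the gain.

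A reader might also infer three stronger things:
- **That baseline imbalance is left uncorrected.** It is not. These outcomes are defined as changes, so baseline is used, but with the wrong weight unless β is near 1.
- **That patients with a missed visit are lost from the analysis.** The article does not describe missing-data handling for these outcomes, and its 20% drop-out figure is a sample-size allowance for the primary endpoint.
- **That a repeated-measures mixed model is plainly the answer.** Over 36 months in this population it raises the question of values truncated by death, which needs a separate decision.

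**Conclusion.** The point holds as a minor one. For the continuous change outcomes, the article fixes an analysis that is valid but generally less precise than baseline adjustment, and one that over-corrects for chance imbalance when the slope is below 1. Under equal SDs and an assumed r of 0.3 to 0.8, the avoidable share of the variance is 35% down to 10%. It can be nil, as at r = 0.5 with a follow-up SD twice the baseline SD. These percentages illustrate a range and are not properties of this trial.

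The formulas apply to the t-test. The loss for the Mann–Whitney test was not computed, and the formulas do not carry over to Rutherford category, which is ordinal. The log-rank test of the primary endpoint, the Farrington–Manning test of the key secondary endpoint and the sample size are unaffected.

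**What to change.** For change in ABI, TBI, EQ-5D-3L index, VascuQuol score and walking distance, make the main analysis at each visit an ANCOVA with treatment arm and the baseline value of the same measure. Report the adjusted difference with its confidence interval. For walking distance, if skewed, use a rank-based or transformed-scale version chosen in advance. Keep the t-test or Mann–Whitney test on change as a sensitivity analysis. Record the choice in the SAP before these outcomes are compared by arm.

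The cost is a few lines of SAP wording and a little more analysis work. All the baseline values are already scheduled.

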## Discussion

The randomized controlled LIMES study was designed to evaluate efficacy and safety of the MAGIC Touch PTA sirolimus-coated balloon catheter for the treatment of infra-popliteal arteries in patients with CLTI. Long-lasting patency and sufficient limb perfusion are essential for limb salvage and survival.

Although the combination of balloon angioplasty and local antiproliferative therapy appears promising, the efficacy of paclitaxel-coated balloons for the treatment of infra-popliteal lesions is still conflicting [9, 13, 14]. In addition, concerns about long-term safety of paclitaxel-coated devices are not dispelled so far. Thus, since challenges related to the coating technology are mastered, sirolimus is suspected to turn out as safe and effective alternative to paclitaxel. Sirolimus is a cytostatic, but not, as paclitaxel, cytotoxic drug. It is characterized by a wide therapeutic window. Phospholipid carriers ensure an improved adhesion to the balloon surface to prevent drug loss into the blood stream. The excipient should ensure an effective transfer of sirolimus into deeper vessel layers where it retains for as long as necessary to inhibit neointima formation [23].

The LIMES study will provide data on patency, clinical improvement, wound healing, health-related quality of life, recurrent revascularization, amputation, and mortality throughout 36 months.

Sirolimus could be suitable to effectively support angioplasty without reducing safety or impede possible later surgical intervention. If sirolimus-coated balloon angioplasty will prove to be effective regarding patency and non-inferior to POBA regarding safety, it may replace POBA where needed and serve as an alternative to paclitaxel-coated balloon angioplasty.

## Abbreviations

ABI: Ankle-brachial index
BMS: Bare metal stent
CLTI: Chronic limb-threatening ischemia
DAPT: Dual antiplatelet therapy
DCB: Drug-coated balloon
DES: Drug-eluting stent
DUS: Duplex ultrasonography
ITT: Intention to treat
MALE-POD: Major adverse limb events and perioperative death
PAD: Peripheral artery disease
POBA: Plain old balloon angioplasty
TBI: Toe-brachial index
TLR: Target lesion revascularization
TVR: Target vessel revascularization
WIfI: Wound, Ischemia, and foot Infection classification
